### 9.5. Statistical methods

Efficacy analyses will be done using the **Per protocol population**. Safety analyses will be performed on the **Safety population**.

- ◆ Frequency tables will be tabulated (by treatment group or otherwise) for all categorical variables by the levels of the variables. Continuous variables (for example age, dose etc) are presented using the

median and range (minimum, maximum) or mean (variance) depending whether the distribution appears symmetrical.

- ◆ Baseline demographic characteristics of the **Per protocol population** will be summarized according to common reporting standards (following CONSORT-guidelines 2010, where applicable). Proportions will be presented together with 85% as well as 95% confidence intervals (CIs).
- ◆ Description of number of cycles of therapy and dose modifications for both the induction treatment as well as the treatment with atezolizumab (**Per protocol population**)
- ◆ Activity of atezolizumab plus carboplatin will be studied in the **Per protocol population** as described above by calculating the proportion of patients free of progression at 24 weeks (PFS according to RECIST (primary endpoint)). Spiderplots and swimmerplots will be used to illustrate the magnitude and duration of response.
- ◆ Activity of atezolizumab will be studied in the **Per protocol population** as described above by calculating ORR and clinical benefit (secondary endpoints) as defined by RECIST. Proportions will be presented together with 85% as well as 95% confidence intervals (CIs).
- ◆ Safety analyses will be performed on the **Safety population**. The worst toxicity grade over all cycles according to the CTCAE criteria version 4.03 will be displayed.
- ◆ For exploratory analyses, means will be compared using either student t-test if validity conditions are fulfilled or using non parametric Wilcoxon-Mann-Whitney tests. Proportions will be compared using either Chi2 statistics or Fisher's exact test depending on validity conditions.

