| Adverse events                               |                |                | x              | x              | x              | x              | x       | x              | x              | x              | x              | x              | x       | x               |                                               |                |          |
| Survival and subsequent treatment                         |                |                |                |                |                |                |         |                |                |                |                |                |         |                 |                                               |                | x        |
| Optional: stool for microbiome analysis                   |                | x  |                | x  |                |                |         |                |                | x  |                |                |         |                 |                                               |                |          |

- 1 3x 16G biopsies: 1 for FFPE, 2 for frozen. Aim at taking sequential biopsies from same lesion
- 2 Mandatory: sufficient number of tumor cells ( $\geq 100$ ) has to be present before patient can enter the study
- 3 Optional
- 4 PBMCs, serum, ctDNA, cfDNA, tumor-educated platelets. At baseline only; material for normal germline DNA. Before cycle 5 and 7 (optional for other centers than the NKI).
- 5 At NKI: material for Breast Immuno Flow (real-time comprehensive analyses off immune cell subpopulations including myeloid cells, [name] lab)
- 6 Every 6 weeks, after 6 months every 9 weeks
- 7 Every 8 weeks, after 6 months every 12 weeks
- 8 Hb, leukocytes incl differentiation, platelets, creat, glucose, urea, sodium, potassium, magnesium, calcium, chloride, bilirubin, gGT, AF, AST, ALT, LDH, CRP, phosphate, albumine
- 9 Hb, leukocytes incl differentiation, platelets, creat, urea, sodium, potassium, calcium, bilirubin, gGT, AF, AST, ALT, LDH
- 10 CA15.3, CEA, TSH, fT4, cortisol, ACTH, amylase, lipase, E2, FSH, LH
- 11 AEs will be graded according to CTCAE 4.03, SAE need to be reported up to 30 days post last atezolizumab study medication infusion
- 12 at baseline full examination, including weight and height, blood pressure, pulse and WHO performance status. During follow-up symptom directed
- 13 only in women of child birth potential

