### 9.2 Sample size

For metastatic ILC patients who are refractory to endocrine treatment, no first or second line 'standard' therapies have been defined. Frequently used anticancer agents are capecitabine, or a taxane. The median PFS reached with these therapies typically lies between 2-4 months, but limited data are available. [25, 26] For this study, it is determined that a regimen that is likely to yield a proportion of patients that is free of progression at 24 weeks of more than 25% should be further explored in a randomized study.

Simon's two-stage (minimax) design will be used.[22] The null hypothesis that the true proportion of patients that is free of progression at 24 weeks is  $\leq 10\%$  will be tested against a one-sided alternative of at least 25%. In the first stage, 22 patients will be accrued. If there are 2 or fewer patients free of progression at 24 weeks in these 22 patients, the study will be stopped or another immunomodulatory drug will be added (agent to be determined). Otherwise, 18 additional patients will be accrued for a total of 40. The null hypothesis will be rejected if 8 or more patients out of those 40 are free of progression at 24 weeks. This design yields a type I error rate 0.04 and power of 80% when the true proportion of patients free of progression at 24 weeks is 25%.

In conclusion, in the run-in phase I part six patients will be included (3+3). In the first stage 22 (including the first n=6 from the run-in phase I part) patients will be included. If 3 or more patients are free of progression at 6 months (see statistics section below), an additional 18 subjects will be entered. Total= 22+18=40. For evaluation of efficacy according to the Simon's two-stage design we will use all patients who received at least 1 cycle of atezolizumab (per protocol population).

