### Translational research objectives (Exploratory objectives)

- ◆ Analyze the increase in immunogenicity after immune response induction treatment using carboplatin using pre-treatment biopsies/blood samples and biopsies/blood samples taken after 2 cycles of carboplatin before the start of atezolizumab. Potential markers to assess immunogenicity: TILs, PD-L1, CD8, FOXP3, CD68 (IHC), changes in gene expression with an emphasize on IFN $\gamma$ -related gene signatures [18, 19, 21], serum cytokine levels, proportion of effector T cells and myeloid subpopulations in peripheral blood [20] (in collaboration with [name] and the [name] labs). Given that certain potentially highly important myeloid immune cell subset might not be viable after biobanking, we will perform flow cytometry within a couple of hours after blood draw ([name] lab. 'Breast Immuno Flow').
- ◆ Comprehensive analyses of responding and non-responding cases using potential predictive markers such as but not limited to TILs, PD-L1 (according to the algorithm of Roche diagnostics), CD8, CD68, number of neoantigens, IFN $\gamma$ -related gene signatures and serum LDH
- ◆ Exploring the role of circulating tumor DNA (ctDNA) cell free (cfDNA) during the discovery of potential predictive biomarkers (Erasmus MC). See section on ctDNA and cfDNA below.
- ◆ Exploring the role of gut microbiota composition and response to immunotherapy. See section on gut microbiome below.
- ◆ Biobanking of tumor tissues (frozen and FFPE), serum and whole blood. All collected at baseline, after induction/before start atezolizumab cycle 1 and before cycle 3, 5 and 7 for the purpose of retrospective analyses of candidate biomarkers or experiments to gain insight into response to immunotherapy in ILCs. See section on biobanking below.

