#### 1. Tumorbiopsies (3x16G) at baseline, before start atezolizumab(=after 2 cycles of carboplatin) and after 2 cycles of atezolizumab

##### 1.1 FFPE (formalin fixed paraffin embedded) tissue (1 biopsy), to analyze:

- ◆ percentage of TILs in the tumor[52, 53], percentage of TILs in the stroma [52, 53],
- ◆ multiplex immunofluorescence: percentage and location membranous PD-L1 expression [54], number and location of FOXP3+ Tregs [55, 56], the ratio of CD8/CD4+ T cells [52, 53], number and location of macrophages and changes in myeloid derived suppressor cells (MDSCs). Pre- and post-treatment samples will be compared. Absolute and relative changes will be described.

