##### 1.2 Fresh Frozen Tissue (2 biopsies), to analyze:

- ◆ DNA for exome-sequencing for the detection of the mutational load, neo-antigens [57] and specific mutations associated with response to atezolizumab in ILCs. It also allows the evaluation of changes in the intratumoral TCR repertoire.
- ◆ RNA for gene expression: Compare patterns of gene expression signatures in pre- and post-treatment samples. Candidate gene expression signatures to evaluate are the interferon-gamma/CD8 gene set as presented by Herbst and further developed by Fehrenbacher and colleagues. This signature is clearly associated with response to atezolizumab in NSCLC [18, 19] Other gene signatures of interest: IgG/lymphocyte-specific kinase metagene [58] as well as the immune-relevant metagenes. [59, 60] We hypothesize that immune-related gene expression signatures will change significantly after a) induction treatment with carboplatin, as well as after b) start of atezolizumab. Exploratory unsupervised analyses will be performed. Evaluation of immune cytolytic activity 'CYT' [61] will yield insight in the magnitude of immunoediting in tumors.

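### Section 9.5 names no paired test for the before/after biomarker comparisons within patients; Mann-Whitney, Chi2 and Fisher assume independent groups and would be conservative and lose power there

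*Protocol*

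**What the plan says.** Section 9.5 has a single bullet on tests for exploratory analyses. For means: "For exploratory analyses, means will be compared using either student t-test if validity conditions are fulfilled or using non parametric Wilcoxon-Mann-Whitney tests". For proportions: "Proportions will be compared using either Chi2 statistics or Fisher's exact test depending on validity conditions". It does not distinguish comparisons between groups of patients from comparisons between time points in one patient.

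Sections 3.3 and 10 then list the exploratory objectives. The first is a before/after question: "Analyze the increase in immunogenicity after immune response induction treatment using carboplatin using pre-treatment biopsies/blood samples", set against samples taken after two carboplatin doses and before atezolizumab starts. The second compares different patients: "Comprehensive analyses of responding and non-responding cases using potential predictive markers".

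The Biobanking part of Section 10 adds detail. For FFPE tissue (item 1.1): "Pre- and post-treatment samples will be compared. Absolute and relative changes will be described". For frozen tissue (item 1.2): "We hypothesize that immune-related gene expression signatures will change significantly after a) induction treatment with carboplatin", and likewise after the start of atezolizumab. The samples are meant to be matched as closely as possible; a footnote to the table in Section 7.5 reads "Aim at taking sequential biopsies from same lesion".

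**The concern.** Mann-Whitney, Chi2 and Fisher's exact test all derive their null distribution from two unrelated sets of patients. In serial samples from one patient, the spread between patients in TILs, PD-L1 or a gene signature is largely common to both samples and cancels in the difference. A test that ignores the pairing counts that spread as error. Its true type I error then falls below the nominal level, and so does its power.

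At stake is the reading of the induction phase. The idea that carboplatin raises immunogenicity is part of the rationale in Sections 1 and 2, and Section 5 makes the repeat biopsies mandatory. If 9.5 were followed literally, real changes in tissue obtained at some burden to patients could go undetected.

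**Working it through.** **1. Questions against named tests.**

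| Comparison | Where | Samples | Do the tests in 9.5 fit? |
|---|---|---|---|
| Responding vs non-responding | Sections 3.3, 10 | different patients | yes |
| IR vs non-IR profile | Sections 3.4, 10 | different patients | yes |
| Before vs after carboplatin induction | Sections 3.3, 10 | same patient | Mann-Whitney, Chi2, Fisher: no; t-test: only if paired |
| Before vs after start of atezolizumab | Section 10, items 1.1 and 1.2 | same patient | as above |

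No paired t-test, signed-rank test, McNemar test or mixed model is named in the protocol.

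**2. The plan's own figures.** Section 9.2 states error and power only for the primary endpoint. With a stop at 2 or fewer of 22 and rejection at 8 or more of 40, the rejection probability is the sum over x = 3 to 22 of P(X = x in 22) × P(at least 8 − x in 18). It gives 0.0398 at 10% and 0.803 at 25%, matching the stated 0.04 and 80%. That design is unaffected. It matters here only for the number of pairs: "Otherwise, 18 additional patients will be accrued for a total of 40" sets the planned ceiling at 40, or 22 if the trial stops after stage 1.

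**3. Effect of ignoring the pairing.** The following are assumptions, not protocol figures: two-sided 5%, normal data, equal SD σ at both times, pre/post correlation ρ, true shift d in SD units.

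- True variance of the mean difference over n pairs: 2σ²(1 − ρ)/n.
- Variance used by an unpaired t-test: 2σ²/n.
- Approximate type I error of the unpaired t-test: 2Φ(−c/√(1 − ρ)), where c = 1.99 for n = 40. At ρ = 0.5: 2Φ(−2.81) ≈ 0.5%. Simulation gives 0.6%, against 5% nominal.
- Unpaired power at d = 0.5, n = 40, ρ = 0.5: Φ((0.5/√(2/40) − 1.99)/√0.5) = Φ((2.236 − 1.99)/0.707) ≈ 64%. Simulation gives 63%.
- Paired t-test in the same case: noncentrality 0.5 × √40/√(2 × 0.5) = 3.16. Simulated power is 87%.

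**4. Rank tests, 40 pairs, 0.5 SD shift (simulated).**

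| ρ | Mann-Whitney | Signed-rank | Relative loss |
|---|---|---|---|
| 0 | 58% | 57% | none |
| 0.3 | 59% | 74% | (74 − 59)/74 = 20% |
| 0.5 | 61% | 87% | (87 − 61)/87 = 30% |
| 0.6 | 62% | 93% | (93 − 62)/93 = 33% |

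Repeat runs differ by up to about three points.

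**5. When the loss reaches half.**

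- 40 pairs, 0.3 SD, ρ = 0.5, t-tests: 46% falls to 19%, a loss of 59%.
- 22 pairs, 0.5 SD, ρ = 0.6, rank tests: 69% falls to 31%, a loss of 55%.
- 40 pairs, shift set so that the paired t-test has 80% power: the unpaired t-test has 68% at ρ = 0.3, 53% at 0.5 and 25% at 0.7; Mann-Whitney has 65%, 49% and 23%. Here the shift shrinks as ρ rises.
- 40 pairs, shift held at 0.5 SD, ρ = 0.8: 99.8% falls to 69.5%, a loss of 30%. With a shift of this size, higher correlation alone does not reach half.

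**6. Proportions, one illustration.** Marker positivity rising from 25% to 50%, 40 pairs, 3% of patients turning negative: Fisher about 57%, Chi2 69%, exact McNemar about 82%.

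**The case against.** The strongest reply is that the bullet in 9.5 is generic and need not govern the pre/post question. Item 1.1 speaks of describing absolute and relative changes, which are naturally within-patient quantities. Item 1.2 adds unsupervised analyses that 9.5 does not list, so 9.5 is not exhaustive. Mann-Whitney would be valid for comparing change scores between responders and non-responders. Section 10 opens by saying that assays and cut-offs are still unknown, and a statistical analysis plan could supply the paired test.

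Part of this stands: applying the bullet to raw pre and post values is one reading, and it is the literal one. It does not remove the mismatch. The protocol does name tests for exploratory analyses, item 1.2 expects a significant change and so implies a test, and the pairing is already fixed by the biopsy schedule.

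Several stronger readings are not supported:

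- A reader might infer that every named test is unpaired. The t-test's form is not stated; its listing beside Mann-Whitney suggests the two-sample form but does not settle it.
- A reader might call the before/after change the main exploratory question. It is listed first, but nothing ranks it above the others.
- A reader might take the protocol to state a null of no within-patient change, or the first objective to include the sample after two atezolizumab cycles. No null is stated, and that time point comes from items 1.1 and 1.2.
- A reader might expect a loss of half the power or more as the normal case. That needs less favourable assumptions than 40 pairs and 0.5 SD. Sequential biopsies come from the same lesion only preferably (Sections 7.2.2 and 7.2.5), so a high correlation cannot be presumed.

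**Conclusion.** The point holds as a mismatch between a stated method and a listed objective. Three of the four named tests do not suit within-patient comparisons, the fourth is ambiguous, and no paired method is named.

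The loss rests on assumed correlation, effect size and number of complete pairs. At 40 pairs and 0.5 SD it is nil at ρ = 0, about 15 points at 0.3, 26 at 0.5 and 31 at 0.6. It reaches half or more with a smaller effect, fewer pairs, or a higher correlation together with a smaller effect.

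The error is conservative: it makes missed changes more likely and does not add false positives. A non-significant exploratory result would not by itself show that induction has no effect. The primary endpoint, sample size and stage-1 rule are untouched, as is the use of these tests for IR vs non-IR and responder vs non-responder comparisons.

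**What to change.** Split the exploratory bullet in Section 9.5:

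- **Between groups of patients** (IR vs non-IR, responders vs non-responders): keep the t-test or Mann-Whitney, and Chi2 or Fisher's exact test.
- **Between time points in the same patient** (baseline, before atezolizumab cycle 1, before cycle 3): paired t-test or Wilcoxon signed-rank test on within-patient differences, and McNemar's test for paired proportions. Optionally, a mixed model with a patient random effect when all three time points are used.

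This costs a sentence or two in 9.5, repeated in the statistical analysis plan if there is one. It needs no further patients, samples or procedures.

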## 9.6 Stopping rules

See dose-limiting toxicity at section 4.

## 10 Translational research

To facilitate development of innovative immunotherapy approaches there is a need to develop and validate tools to identify patients who can benefit from immunotherapy. Despite substantial effort, it is not yet known which parameters of antitumor immunity to measure and which assays are optimal for those measurements. Consequently, at the time of writing of the protocol, it is unknown which assays, validation techniques and cut-offs will be used for the final analyses.

### Secondary research objective:

- ◆ Proportion of patients free of progression (RECIST 1.1[16]) at 6 months in the IR-profile subgroup vs the non-IR-subgroup as defined by gene expression profiling. See section on gene expression profiling below.

### Translational research objectives (Exploratory objectives)

- ◆ Analyze the increase in immunogenicity after immune response induction treatment using carboplatin using pre-treatment biopsies/blood samples and biopsies/blood samples taken after 2 cycles of carboplatin before the start of atezolizumab. Potential markers to assess immunogenicity: TILs, PD-L1, CD8, FOXP3, CD68 (IHC), changes in gene expression with an emphasize on IFN $\gamma$ -related gene signatures [18, 19, 21], serum cytokine levels, proportion of effector T cells and myeloid subpopulations in peripheral blood [20] (in collaboration with [name] and the [name] labs). Given that certain potentially highly important myeloid immune cell subset might not be viable after biobanking, we will perform flow cytometry within a couple of hours after blood draw ([name] lab. 'Breast Immuno Flow').
- ◆ Comprehensive analyses of responding and non-responding cases using potential predictive markers such as but not limited to TILs, PD-L1 (according to the algorithm of Roche diagnostics), CD8, CD68, number of neoantigens, IFN $\gamma$ -related gene signatures and serum LDH
- ◆ Exploring the role of circulating tumor DNA (ctDNA) cell free (cfDNA) during the discovery of potential predictive biomarkers (Erasmus MC). See section on ctDNA and cfDNA below.
- ◆ Exploring the role of gut microbiota composition and response to immunotherapy. See section on gut microbiome below.
- ◆ Biobanking of tumor tissues (frozen and FFPE), serum and whole blood. All collected at baseline, after induction/before start atezolizumab cycle 1 and before cycle 3, 5 and 7 for the purpose of retrospective analyses of candidate biomarkers or experiments to gain insight into response to immunotherapy in ILCs. See section on biobanking below.

### Gene expression profiling

Recently, at our institute, a large scale genomic analysis of ILC identified an **immune related (IR) subtype** within ILCs characterized by mRNA up-regulation of CD4, CD8, PD-L1, PD1 and CTLA4 and greater sensitivity to DNA-damaging agents. [9] In line with this, researchers from The Cancer Genome Atlas (TCGA) have shown that immune-related genes (interleukins, chemokines, MHC complex, IDO1 and IFN $\gamma$ ) are highly expressed in a subset of ILC tumors. [10] This suggests that this IR-subtype that it is more likely that in these tumors a pre-existing anti-cancer T cell response is present and that PD1-blockade might be more effective in these cases. To test this hypothesis we conducted this exploratory phase II GELATO study. Within this study, gene expression profiling using frozen biopsies taken at baseline will be conducted using Agilent arrays at the laboratory of Agendia BV. To classify a tumor into IR-related or non-IR-related, the genelist generated by the RATHER consortium will be used. [9]

## **ctDNA and cfDNA**

Mutations and rearrangements provide promising markers for patient-specific disease monitoring in cell free DNA (cfDNA) present in the circulation. This cell free DNA contains tumor DNA (ctDNA) which represents a very attractive and sensitive option to establish mutational changes occurring in tumor cells in a minimal invasive manner. For instance in patients with metastatic breast cancer mutations in the estrogen receptor (ESR1) are rarely detected in primary tumors but are frequently reported in plasma from patients with metastatic disease with acquired resistance to aromatase inhibitors. In the Erasmus MC, ample experience exists with regard to sensitive mutation profiling of ctDNA using digital PCR (see figure below) or targeted sequencing. Next to ctDNA, cfDNA can also contain DNA from various immune-related cells such as T-cells and genetic changes in these cells could also be monitored. Genetic aberration in ctDNA which may provide early markers for immune response and may improve insight in combination strategies, may be monitored during disease progression and may thus guide treatment decisions in future studies

Primary endpoint of this side study: assessment of patient-specific mutations in E-cadherin, the driver in ILC, as an early response marker to the combination treatment.

Secondary endpoint(s) of the side study: i) assessment of mutations in E-cadherin as a marker to monitor disease progression, ii) assessment of the changing landscape of somatic mutations in ctDNA (by targeted or genome-wide NGS analysis) during combination treatment, iii) exploratory analysis of TCR rearrangements in cfDNA at progression on the combination treatment.

